### Safety and tolerability in healthy volunteers and glaucoma patients during 24-hour continuous IOP recording – investigation 09/02

The primary endpoint in this trial was level of discomfort associated with SENSIMED Triggerfish^®^ in the installed eye at 24 hours, measured by a Visual Analog Scale (VAS from 0 to 100, 0 meaning no discomfort, 100 meaning intolerable). Two populations were included using a 1:1 ratio: Subjects with glaucoma and a similar group of healthy subjects.

All subjects underwent an ophthalmological examination including objective and subjective refraction tests, best corrected visual acuity, topography, pachymetry, slit lamp examination and Goldmann tonometry, before and after SENSIMED Triggerfish^®^ recording. Slit lamp findings (lid erythema, lid edema, conjunctiva erythema, conjunctiva edema, corneal staining and intraocular inflammation) were graded according to scales. Visual acuity was assessed using early diabetic treatment retinopathy study (EDTRS) charts.

AEs for slit lamp findings were recorded whenever a progression of 2 grades or more over 24 hours was observed. Visual acuity reduction was recorded as an AE whenever a reduction of 15 letters (3 lines) or more was observed.

All but 2 of the 40 subjects completed the full 24 hours of SENSIMED Triggerfish^®^ wearing. One glaucoma subject dropped out due to improper device fitting and one healthy subject dropped out due to device being too big.

No significant baseline differences, for gender, age or GAT- IOP were found between the two study groups.

The mean time of SENSIMED Triggerfish^®^ wearing was 23 hours for both study groups.

There were no SAE’s reported, but there were some device related AE’s:

85% of the glaucoma subjects (17/20) and 75% of the healthy subjects (15/20) experienced an adverse event that was probably or definitely device related to study device. Only a small portion of these device related adverse events were deemed severe (20% for glaucoma and 5% for healthy subjects).

There were no significant differences between healthy and glaucoma subjects on VAS when tested using an independent groups Wilcoxon rank sum test with α = 0.10 (p = 0.41), so that the two groups were combined for describing VAS. Median VAS (combined group) was 19, with 53% of subjects at 20 and below. The mean VAS score was 24.33.

The secondary endpoints included ophthalmologic, slit lamp and GAT-IOP examination of the study eye.

Significant changes from baseline to after SENSIMED Triggerfish^®^ recording were found for the following ophthalmic parameters: corneal topography horizontal, objective refraction – cyl, objective refraction – sph, objective refraction – degree, subjective refraction – cyl, subjective refraction – sph, subjective refraction – degree and visual acuity; and for the following slit lamp parameters: conjunctiva edema, conjunctiva erythema, epithelial defects and lid edema. There was no significant change from baseline in GAT-IOP.

In conclusion the two study groups (glaucoma and healthy Subjects) may be combined in terms of assessing SENSIMED Triggerfish^®^ tolerability.

SENSIMED Triggerfish^®^ was well tolerated over the 24-hour study period and caused no Serious Adverse Events (SAE’s).

# Design of the clinical investigation

## Title of the investigation

Efficacy of 24-hour intraocular pressure fluctuation recording with the SENSIMED Triggerfish^®^ contact lens sensor

## General

This is a prospective, open-label cohort investigation.

### Safety endpoints

Adverse events (AE's) including serious AE's (SAE's), including severity, occurring at any time during the trial or follow up, whether or not deemed related to study device. Safety measurements will include standard slit-lamp examination.

### Primary efficacy endpoints

This study has the following two, co-primary TF endpoints for each subject:

1. Linear correlation between Time and Continuous TF recordings from approximately 4 hours preceding going to bed to 4 hours after. Relationship between TF recordings and Time will be obtained by modelling the former against the latter using a second order polynomial^[[1]](#footnote-1)^. Linear correlation between TF recordings and Time is the standardized β obtained from the model.
2. Percent difference between frequency of ocular pulsation and HR scored dichotomously.

### Secondary efficacy endpoints

Secondary efficacy endpoints include, for each subject:

- Subject Acceptance of TF, which will be measured on a 5 point visual analog scale (VAS) where 5, indicates high acceptance of TF and 1 indicates low acceptance.
- Categorization of subject diurnal rhythm of IOP as measured by TF and assignment to pre-specified diurnal rhythms identified from the literature.

### Performance endpoint

- Validity of TF recording at the interval and subject levels scored dichotomously:
  - 0 – invalid
  - 1 – valid

### Equipment and methods

Investigational data will be collected during patient visits and hospitalisation on site. All investigation related data will be recorded on CRFs. Delegated site personnel will be instructed to complete the CRFs after each visit. All investigational data will be analyzed 6 weeks after Last Patient Last Visit (LPLV).

All equipment used in this investigation is standard ophthalmology service equipment. Calibration and other equipment maintenance will be done at regular intervals as specified by site procedures. Equipment to be used in the study will be listed and maintained as a separate document. All tonometers used in this investigation will be calibrated.

IOP measurements will be assigned randomly to experienced researchers, adopting working schedule to avoid fatigue. Inter-operator IOP variability will be verified to be insignificant prior to the study. The same equipment (instruments) will be used for all patients.

Proparacaine will be used as corneal anaesthesia.

### Device exposure

The planned exposure time to SENSIMED Triggerfish is 24 hours ± 1 hour during one IOP fluctuation recording session. This includes 24-hour active IOP fluctuation recording and additional time necessary for the fitting control plus some variation due to logistic reasons.

# Subjects

The investigation will recruit male and female patients 18-80 years old and either diagnosed with primary open-angle glaucoma, including normal tension glaucoma or being healthy subjects including subjects with ocular hypertension.

30 eyes of 30 subjects showing at least 3 mmHg difference between wake and sleep IOP, as calculated as the mean of IOP during the 4 hours preceding and following going to bed, respectively, will be enrolled in the investigation.

Patients will be considered enrolled in the study upon signature of informed consent. A screening visit and one 24-hour IOP fluctuation recording session are planned for each patient. IOP fluctuation recording sessions will be carried out in a sleep unit. The expected duration of participation for each patient of 2 days over two to three weeks.

Patients will be recruited over a 6-month period. The total expected study duration is 6 months.

## Patient withdrawal and replacement

Patients will be immediately withdrawn from the study in the case of revoked consent or, in the investigator’s opinion, withdrawing the patient is in the patient’s best interest. If informed consent is revoked prior to device installation, the subject will be replaced.

If no Sensor (maximum two attempts with different Sensor sizes) can be adapted to the subject, no recording will be carried out and the Sensor removed from the eye of the subject. The subject will be withdrawn from the study and replaced.

Patients experiencing device-related Serious Adverse Events will be withdrawn from the study. With the consent of the patient, the 24-hour recording session will be repeated in case of device failure.

In all cases of patient withdrawal, the patient will receive a final ophthalmological examination as stated in 7.4. Inclusion / exclusion criteria.

### Inclusion criteria

Subjects must correspond to all other inclusion criteria in order to be eligible for the investigation.

- Signed informed consent for the investigation
- Diagnosis of primary open angle glaucoma (POAG), including normal tension glaucoma, or healthy subjects, including subjects with ocular hypertension for whom no evidence or suspicion of structural or functional glaucomatous damage exists
- No anti-glaucomatous drug treatment or washed-out for 4 weeks
- IOP symmetry of +/- 3 mmHg between fellow eyes
- Age 18–80 years
- Not more than 4 diopters spherical equivalent on both eyes
- Not more than 2 diopters cylinder equivalent on both eyes
- For women of childbearing potential, adequate contraception

### Exclusion criteria

Subjects presenting with any of the following criteria will not be included in the trial:

- Patients who have had ocular surgery within the last 3 months.
- Corneal or conjunctival abnormality hindering contact lens adaptation
- Wear of full frame metallic glasses during SENSIMED Triggerfish^®^ monitoring
- Severe dry eye
- Secondary forms of open angle glaucoma (OAG)
- Allergy to corneal anesthetic
- Patients with contraindications for silicone contact lens wear
- Pregnancy and lactation
- Patients not able to understand the character and individual consequences of the investigation
- Simultaneous participation in other clinical research

No patient will be allowed to participate in this trial more than once.

# Procedures

Patients accepting signing informed consent will receive screening procedures to determine their eligibility for the investigation. All eligible patients will be enrolled and receive IOP fluctuation recording during 24 hours. Left and right eyes will be recorded randomly.

## Baseline visit

Following the signature of informed consent, the procedures listed hereunder will be carried out on the study eye.

- Demographic data
- Medical and surgical history
- Concomitant medication and procedures
- Automated objective refraction test
- Best corrected visual acuity (BCVA)
- Slit lamp examination
- TBUT
- Corneoscleral profile evaluation
- Topography/keratometry
- Pachymetry
- Goldmann applanation tonometry (three readings) and pneumatonometry in each eye
- For women of childbearing potential, pregnancy test
- Inclusion and exclusion criteria

For GAT, one drop of proparacaine will be instilled in the eye prior to the measurement. The three readings will be taken within at one-minute intervals.

IOP will be measured by GAT and pneumatonometer in the sitting position in both eyes. Then, the subjects will lie down for at least 15 minutes and the IOP will be measured with the pneumatonometer in both eyes.

A baseline evaluation of the corneoscleral profile and topography/keratometry will be done to determine the appropriate Sensor base curve for the patient, according to the SENSIMED Triggerfish^®^ User Manual.

## Circadian synchronization

7 days prior to the IOP fluctuation recording, subjects will adopt a regular dark-sleep cycle close to 11 PM to 7 AM, with a maximum deviation of 1 hour. Subjects will be monitored for light exposure and physical activity. In addition, they will keep a sleep-wake diary.

All subjects will be instructed to abstain from alcohol for 3 days and caffeine for 1 day before the IOP fluctuation recording and not to wear contact lenses within the 24 hours preceding Day 1.

## Day 1

Subjects will enter the sleep unit at 2 PM ± 2 hours.

The following procedures will be carried out prior to IOP fluctuation recording:

- Best corrected visual acuity (BCVA)
- Slit lamp examination
- Pachymetry
- Goldmann applanation tonometry (GAT, three readings in each eye)
- Concomitant medication and procedures
- Adverse events and complaints

Prior to GAT, one drop of proparacaine will be instilled in the eye. The three tonometric measurements will be done at one-minute intervals.

The three reference GAT IOP measurements will be done in each eye immediately prior to the installation of the SENSIMED Triggerfish^®^ Sensor in one eye by the Investigator or delegated staff. Left and right eyes will be selected based on randomization.

If the Sensor base curve selected for the patient in line with the SENSIMED Triggerfish^®^ User Manual does not adapt appropriately to the patient’s eye, the initially selected Sensor may be removed and an attempt with a Sensor of different base curve done. A Sensor with the base curve expected to yield appropriate adaptation will be selected for the second attempt. The investigator will not attempt to install more than two Sensors to the same eye of a patient or healthy subject. The Sensor showing the better adaptation on the patient’s/healthy subject eye will be used for the recording. The other Sensor will be discarded. Any recording done with a Sensor having a base curve other than that indicated for the patient in the SENSIMED Triggerfish User Manual should be recorded, with motivation, in the patient’s CRF.

When the adaptation of the Sensor on the patient’s eye is satisfying, the recording will be initiated. The device will be used according to the manufacturer’s instructions.

Subjects will remain inside the sleep unit during the entire study. Light-dark cycles will be controlled and their onset will be individually adapted to match the subjects’ accustomed circadian cycle. Room activities will be taped. Patients will record their activities, environment and any particular events by the means of a multiple choice patient diary at the end of every 30-minute period throughout the recording.

If patients wish to read during the recording session, the reading material should be placed at eye level to assure communication between the Sensor and the Antenna. Full-frame metal glasses are prohibited throughout the recording since they are known to interfere with the device energy and data transfer.

During the IOP fluctuation recording, IOP measurements will be taken in the non-SENSIMED Triggerfish^®^ eye using a pneumatonometer, as follows:

- IOP (fellow eye) every two hours in the sitting position during the wake period
- 30 minutes after bedtime and then every 2 hours in the supine position

In the dark period, IOP measurements will be done in as near total darkness as possible (e.g. under red light intensity < 5 lux). Subjects will be awakened if necessary. At each time point and if needed, a reading will be taken after instillation of proparacaine within a few minutes.

## Day 2

IOP measurements in the fellow eye will be continued:

- Every two hours throughout the dark-sleep period, in supine position
- 30 minutes after waking, is sitting position and then every two hours until the full 24 hours

At each time point, measurements of IOP using the tonometer will be taken after instillation of proparacaine if needed. In the dark period, IOP measurements will be done in as near total darkness as possible. Subjects will be awakened if necessary. After an 8-hour dark-sleep period, lights will be turned on and subjects will be awakened, if needed.

### Ocular pulse assessment

At three times during the sleep period, event-related IOP fluctuation will be assessed. The following assessment will be done:

- Heart rate over 6 minutes

### Final procedures

After 24 hours the IOP fluctuation recording is completed and the device will be removed from the patient by the investigator or delegated staff. Recording data will be downloaded to the investigator’s computer. The following procedures will be carried out in both eyes:

- SENSIMED Triggerfish^®^ removal
- Best corrected visual acuity (BCVA)
- Slit lamp examination
- Pachymetry
- Goldmann applanation tonometry (GAT, three readings in each eye)
- Sleep quality assessment
- Visual analogue scale
- Collection of patient diary
- Concomitant medication and procedures
- Adverse events and complaints

## Procedures to assess safety

In the current investigation safety is assessed through the collection of adverse events and serious adverse events (cf section 8). Conjunctival redness and corneal staining will be graded according to Efron scales. Grades 0, 1 and 2 will be considered normal.

## Procedures to assess efficacy

SENSIMED Triggerfish^®^ efficacy is studied as the primary objective in this investigation. SENSIMED Triggerfish^®^ measures will be compared to parallel IOP measurements on fellow eye.

In addition, secondary efficacy will be investigated by subject acceptance, where subjects will be asked to indicate their acceptance of SENSIMED Triggerfish on a 5-point visual analog scale, where 5 indicates high acceptance and 1 indicates low acceptance.

Moreover, subjects’ diurnal rhythm as recorded with SENSIMED Triggerfish will be categorized according to pre-specified diurnal rhythms identified from literature.

## Procedures to assess performance

Performance is investigated by the dichotomous evaluation of the SENSIMED Triggerfish recording validity, where 0 means invalid recording and 1 valid recording in the current investigation. Non-medical complaints will be collected (cf section 8).

## Procedures carried out by Sensimed representatives

Training on the handling and operation of SENSIMED Triggerfish^®^ will be provided by Sensimed employees or representatives. Sensimed employees and representatives may assist to the installation/removal of SENSIMED Triggerfish^®^ on/from patients or healthy subjects upon agreement with the investigator and will provide technical support, remote or on site, on SENSIMED Triggerfish^®^ throughout the investigation.

## Concomitant medications / treatments / conditions

#### Prior and Concomitant medical conditions

Relevant prior and ongoing (at screening) concomitant medical conditions and procedures will be recorded on the Medical and Surgical history pages of the patient’s CRF. New illness and worsening of ongoing illness will be reported as AE, unless in line with expected disease progression.

### Concomitant Treatments

There are no prohibited treatments in this investigation. Any ongoing or new drug therapy will be recorded on the appropriate pages of the patient’s CRF from the date of informed consent.

## Duration of follow-up

In the case of an ophthalmic adverse event, patient should receive a follow-up ophthalmic examination in order to record the event outcome. Outside this procedure, there is no follow-up planned beyond the IOP fluctuation recording session in this investigation.

# Adverse events, adverse device effects and non-medical complaints

## Adverse Event Definitions

**Adverse event (AE):** Any untoward medical occurrence in a subject.

**Adverse device effect:** Any untoward and unintended response to a medical device.

**Life-threatening adverse event:** Any adverse event that places the subject, in view of the investigator-sponsor, at immediate risk of death from the event as it occurred (i.e., does not include an adverse event that, had it actually occurred in a more severe form, might have caused death).

**Serious adverse event (SAE):** Any adverse event that:

- Led to death
- Led to a serious deterioration in the health of the subject that
- Resulted in life-threatening illness or injury,
- Resulted in permanent impairment of a body structure or a body function ,
- Required in-patient hospitalization or prolongation of existing

hospitalization,

- Resulted in medical or surgical intervention to prevent permanent impairment to a body structure or a body function
- Led to foetal distress, foetal death or a congenital abnormality or birth defect

**Serious adverse device effect:** Adverse device effect that has resulted in any of the consequences characteristic of a serious adverse event or that might have led to any of these consequences if suitable action had not been taken or intervention had not been made or if circumstances had been less opportune.

*Hospitalization* shall include any initial admission (even if less than 24 hours) to a healthcare facility as a result of a precipitating clinical adverse event; to include transfer between hospital and intensive care unit. Hospitalization or prolongation of hospitalization in the absence of a precipitating, clinical adverse event (e.g. for a preexisting condition not associated with a new adverse event or with a worsening of the preexisting condition; admission for a protocol-specified procedure) is not, in itself, a serious adverse event.

**Unanticipated adverse device effect:** any serious adverse effect on health or safety or any life-threatening problem or death caused by, or associated with, a device, if that effect, problem, or death was not previously identified in nature, severity, or degree of incidence in the investigational plan or application (including a supplementary plan or application), or any other unanticipated serious problem associated with a device that relates to the rights, safety, or welfare of subjects.

## Complaint definition

**Complaint:** Written, electronic or oral communication that alleges deficiencies related to the identity, quality, durability, reliability, safety or performance of an investigational device. These can include complaints that might have led to a medical occurrence if a) suitable action had not been taken or b) intervention had not been made or c) if circumstances had been less fortunate.

NOTE: Complaints involving a medical occurrence are handled under the adverse event system (cf section 8.1;8.3-8.7).

## Eliciting Adverse Event Information

Clinical study patients will be routinely questioned about adverse events at study visits.

## Recording and Reporting of Adverse Events

All observed or volunteered adverse events (serious or not) and abnormal test findings, regardless of treatment group, if applicable, or suspected causal relationship to the investigational device or, if applicable, other study treatment or diagnostic product(s) will be recorded in the subjects’ CRF. For all adverse events, sufficient information will be pursued and/or obtained so as to permit 1) an adequate determination of the outcome of the effect (i.e. whether the event should be classified as a serious adverse event) and 2) an assessment of the causal relationship between the adverse event and the investigational device or, if applicable, the other study treatment or diagnostic product(s).

Adverse events felt to be associated with the investigational device will be followed until the event (or its sequelae) or the abnormal test finding resolves or stabilizes at a level acceptable to the investigator or until 30 days after the subject’s last exposure to the investigational device, whichever comes first.

### Reporting of Serious Adverse Events (SAE), Serious Adverse Device Effects (SADE) and Unanticipated Serious Adverse Device Effects (UADE)

All SAEs, SADEs and UADEs are to be immediately (without undue delay and no later than 24 hours) reported to Sensimed AG, using the AE Report Form, when gaining knowledge of the event:

SENSIMED AG

Email: [contact]

SADEs and UADEs are to be reported, by the investigator, to the competent Ethics Institutional Review Board (IRB), within 10 days of gaining knowledge of the event if there is a possible, probable or definite causal relationship with the investigational device.

### Reporting of Adverse Device Effects (ADE)

All ADEs are to be reported to Sensimed AG, using the appropriate form, within 7 days of gaining knowledge of the event, to:

SENSIMED AG

Email: [contact]

## Abnormal test findings

Abnormal baseline values and conditions will not be considered as adverse events. Any change in test findings and pre-existing conditions during the investigation will be considered adverse events and reported as such, provided that they are judged clinically significant by the investigator and unless an expected evolution of the condition in question.

## Causality and severity assessment

The investigator will promptly review documented adverse events (AE) and abnormal test findings to determine 1) if the abnormal test finding should be classified as an adverse event; 2) if there is a reasonable possibility that the adverse event was caused by the investigational device; and 3) if the adverse event meets the criteria for a serious adverse event.

For each adverse event, the investigator will evaluate the causality relationship between the investigational device and the observed adverse event. The relationship between the adverse event and the investigational device will be recorded as either of the following:

- Unrelated – the AE has no temporal (timing) relationship to the intervention and is not related to the investigational device
- Unlikely related - the AE has no temporal relationship to the intervention and is unlikely related to the investigational device
- Possibly related - the AE has a reasonable temporal relationship to the intervention and may be related to the investigational device.
- Probably related - the AE has a reasonable temporal relationship to the intervention and is likely related to the investigational device.
- Definitely related - the AE has a reasonable temporal relationship to the intervention and is clearly related to the investigational device.

If the investigator’s determination of causality is “possibly related”, “probably related” or “definitely related”, the adverse event will be classified as associated with the use of the investigational device for reporting purposes. If the investigator’s determination of causality is “unrelated” or “unlikely related”, the event will be considered as not associated with the use of the investigational device.

Severity is rated according as mild, moderate or severe:

- Mild: Symptom(s) barely noticeable to the patient or does not make the patient uncomfortable. The AE does not influence performance or functioning. Prescription drugs are not ordinarily needed for relief of symptom(s).
- Moderate: Symptom(s) of a sufficient severity to make the patient uncomfortable. Performance of daily activities is influenced. Treatment of symptom(s) may be needed.
- Severe: Symptom(s) of a sufficient severity to cause the patient severe discomfort. Severity may cause cessation of treatment with the drug. Treatment for symptom(s) may be given.

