### Safety

The safety analyses will be descriptive and narrative in nature, with AEs, including serious AEs (SAEs), coded using MedDRA and tabulated by body system, preferred term, group, severity and relation to procedure. Descriptive statistics and shift analysis tables will be provided as appropriate for Ophthalmological examination results.

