### Tonometer

Repeated IOP measurements using any contact tonometer, such as GAT or pneumatonometer, may put the patient at increased risk for ocular complications mainly due to the contact between the tonometer and the cornea. The ocular anesthetic may also provoke side effects.

Anticipated risks are detailed in Part L.

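### The causality scale has no grade for an event that coincides with wear but is not, or probably not, due to the device, and the planned 'relation to procedure' table has no matching rating

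*Protocol*

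**What the plan says.** Section 8.6 (Causality and severity assessment) states that the relationship of each adverse event to the investigational device "will be recorded as either of the following", and lists five grades. The lowest of them is worded "Unrelated – the AE has no temporal (timing) relationship to the intervention and is not related to the investigational device". One step above it, and sharing its condition on timing, stands "Unlikely related - the AE has no temporal relationship to the intervention and is unlikely related to the investigational device".

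The third grade in ascending order is "Possibly related - the AE has a reasonable temporal relationship to the intervention and may be related to the investigational device". *Probably related* and *Definitely related* carry the same timing condition with a stronger statement about cause. For these upper three grades, "the adverse event will be classified as associated with the use of the investigational device for reporting purposes"; the lower two are treated as not associated. The section does not define the intervention to which the timing refers.

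Section 9.8.3 (Safety) plans for adverse events to be "tabulated by body system, preferred term, group, severity and relation to procedure".

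The protocol recognises causes other than the Sensor. Section 12.2.2 (Tonometer) says that repeated contact tonometry "may put the patient at increased risk for ocular complications mainly due to the contact between the tonometer and the cornea", and adds that the anaesthetic may have side effects. Section 15.4 lists ocular events expected from the tonometers, including abrasion, ulcer, pain and conjunctivitis. These also appear in section 15.1 for the Sensor.

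**The concern.** A causality scale should let the investigator separate timing from cause. Here the two are tied together: an event can be graded as not associated only if it has no link in time with the intervention. In this study that condition is hard to meet once the Sensor is in place. Observation centres on one wear session with an examination before and after it (sections 7.3 and 7.4), and section 7.10 plans no follow-up beyond the session except to record the outcome of an ophthalmic event.

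Tonometry and topical anaesthesia fall in the same window. Section 7.3 places three Goldmann readings in each eye, after proparacaine, immediately before the Sensor is fitted. Section 7.4.2 repeats the Goldmann readings after removal. During wear the fellow eye has pneumatonometry every two hours, with proparacaine if needed. An abrasion in the lens eye may come from the lens or from the tonometer; one in the fellow eye cannot come from the lens. Neither event can be graded as not associated if the definitions are followed literally.

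The split into device-associated and not associated is what a reader of a single-arm device study looks for, and three rules in the protocol use it.

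**Working it through.** No sample size, power or alpha figure is involved, and the plan states no number that could be reproduced. The check is logical: cross the two attributes in the definitions and see which combinations are covered.

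Attribute 1 is a temporal relationship to the intervention (no or yes). Attribute 2 is the judged device cause, in the five degrees used in section 8.6. That gives 2 × 5 = 10 combinations.

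| Device as cause | No temporal relationship | Temporal relationship |
| --- | --- | --- |
| Not related | *Unrelated* | no grade |
| Unlikely | *Unlikely related* | no grade |
| May be | no grade | *Possibly related* |
| Likely | no grade | *Probably related* |
| Clearly | no grade | *Definitely related* |

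1. Covered: 2 in the first column and 3 in the second, 5 of 10.
2. Uncovered: 10 − 5 = 5. The three in the first column (no link in time, yet the device may be, is likely to be or clearly is the cause) hardly arise. The two in the second column are events during or next to wear with another, more likely cause.
3. Take an event in one of those two cells. *Unrelated* and *Unlikely related* fail on timing. *Possibly related* fails on cause, because it also requires that the device may be responsible. The list is closed, so no valid grade remains.
4. Section 8.6 contradicts itself here. Before grading, the investigator must decide whether device causation is reasonably possible. For an event during wear the answer may be no, but the scale then has nowhere to record that answer.
5. The undefined term can widen the gap. Section 8.7, in describing protocol-related events, uses intervention for anything the protocol requires. Under that meaning, tonometry and anaesthetic events are always linked in time to the intervention, including those at the baseline visit before any Sensor is worn.
6. Rules that use the split:
   - section 6.1, withdrawal after a device-related serious event;
   - section 8.4, the follow-up of events felt to be device-associated;
   - section 8.4.1, reporting of serious and unanticipated device effects to the review board "if there is a possible, probable or definite causal relationship with the investigational device".
7. Section 9.8.3 set against section 8.6: the table needs relation to procedure, but the rating collected is relation to the device. Section 8.4 asks for enough information to judge causality for other study treatments or diagnostic products where applicable, but gives no scale for them.

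**The case against.** The strongest reply is that this is a wording slip which a competent investigator will work around. *Possibly related* has two conditions, and the reasonable-possibility question comes first, so someone who sees no role for the device is not obliged to choose it. That is right. A reader might infer that tonometry and anaesthetic injuries are forced into the device-associated group; the text does not support this. It leaves a gap that can be resolved either way. Drift upwards is likely where timing decides the choice, but it is not certain.

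A reader might also infer that the safety endpoint itself is misattributed. It is not. Sections 5.2.1 and 9.5.1 count all adverse events regardless of relatedness, and the analysis is descriptive, with no threshold on related events.

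Other limits also stand:

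- Adverse events are collected from the baseline visit. Events before wear can be graded as written if the intervention means the device.
- The review-board trigger covers only serious or unanticipated device effects, and over-reporting these would be the cautious error.
- All five grades are recorded and collapsed only for reporting, so possible can be shown apart from probable and definite without changing the protocol.
- The adverse event form is not shown, so it cannot be said that the affected eye goes unrecorded. If it is recorded, fellow-eye events can be told apart. The harder ambiguity is in the lens eye.

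None of this supplies a valid grade for the two empty cells, or a rating behind the procedure table.

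**Conclusion.** The point holds as a defect in the definitions. In section 8.6, an event linked in time to the intervention but not, or unlikely to be, due to the device has no grade, and section 9.8.3 calls for a relation to procedure that section 8.6 does not rate. The consequence is inconsistent coding of the related/not-related split, probably leaning towards device-associated, and a knock-on effect on the three rules that use it. The total of adverse events and both co-primary efficacy analyses are untouched.

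The size in events cannot be stated. The number of tonometer contacts is not a number of events, and the documents give no rate from which to estimate how many events fall into the gap. Nor do they plan a comparison of related-event rates with the earlier safety and tolerability study, so no bias in such a comparison can be claimed.

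The conclusion assumes that the definitions are applied literally and that no separate instruction to investigators overrides them. It is a modest defect, but worth correcting before enrolment because causality is best judged when the event occurs.

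**What to change.** In section 8.6, remove the absence of a temporal relationship as a required condition of *Unrelated* and *Unlikely related*, so that an event which coincides with wear but has a more likely other cause can be graded there. State whether the intervention means the device or any study procedure. Add a second rating, on the same five grades, for relation to study procedures (tonometry and anaesthetic), and tabulate both ratings in section 9.8.3. Sections 6.1, 8.4 and 8.4.1 should then be checked to confirm that each refers to the device rating.

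The cost is one change of wording and one extra rating on the adverse event form. No examination, visit or subject is added.
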